# Feasibility of a Home-Based Cognitive-Physical Exercise Program in Patients With Chronic Obstructive Pulmonary Disease: Protocol for a Feasibility and Pilot Randomized Controlled Trial

**DOI:** 10.2196/48666

**Published:** 2023-07-12

**Keywords:** pulmonary disease, chronic obstructive, telerehabilitation, physical exercise, cognitive training, randomized controlled trial, pilot study

## Abstract

**Background:**

Chronic obstructive pulmonary disease (COPD) is a progressive condition associated with physical and cognitive impairments contributing to difficulty in performing activities of daily living (ADLs) that require dual tasking (eg, walking and talking). Despite evidence showing that cognitive decline occurs among patients with COPD and may contribute to functional limitations and decreased health-related quality of life (HRQL), pulmonary rehabilitation continues to focus mainly on physical training (ie, aerobic and strength exercises). An integrated cognitive and physical training program compared to physical training alone may be more effective in increasing dual-tasking ability among people living with COPD, leading to greater improvements in performance of ADLs and HRQL.

**Objective:**

The aims of this study are to evaluate the feasibility of an 8-week randomized controlled trial of home-based, cognitive-physical training versus physical training for patients with moderate to severe COPD and derive preliminary estimates of cognitive-physical training intervention efficacy on measures of physical and cognitive function, dual task performance, ADLs, and HRQL.

**Methods:**

A total of 24 participants with moderate to severe COPD will be recruited and randomized into cognitive-physical training or physical training. All participants will be prescribed an individualized home physical exercise program comprising 5 days of moderate-intensity aerobic exercise (30-50 minutes/session) and 2 days of whole-body strength training per week. The cognitive-physical training group will also perform cognitive training for approximately 60 minutes, 5 days per week via the BrainHQ platform (Posit Science Corporation). Participants will meet once weekly with an exercise professional (via videoconference) who will provide support by reviewing the progression of their training and addressing any queries. Feasibility will be assessed through the recruitment rate, program adherence, satisfaction, attrition, and safety. The intervention efficacy regarding dual task performance, physical function, ADLs, and HRQL will be evaluated at baseline and at 4 and 8 weeks. Descriptive statistics will be used to summarize intervention feasibility. Paired 2-tailed *t* tests and 2-tailed *t* tests will be used to compare the changes in the outcome measures over the 8-week study period within and between the 2 randomized groups, respectively.

**Results:**

Enrollment started in January 2022. It is estimated that the enrollment period will be 24 months long, with data collection to be completed by December 2023.

**Conclusions:**

A supervised home-based cognitive-physical training program may be an accessible intervention to improve dual-tasking ability in people living with COPD. Evaluating the feasibility and effect estimates is a critical first step to inform future clinical trials evaluating this approach and its effects on physical and cognitive function, ADL performance, and HRQL.

**Trial Registration:**

ClinicalTrials.gov NCT05140226; https://clinicaltrials.gov/ct2/show/NCT05140226

**International Registered Report Identifier (IRRID):**

DERR1-10.2196/48666

## Introduction

### Background

Chronic obstructive pulmonary disease (COPD) is a progressive respiratory condition characterized by chronic bronchitis and emphysema [1]. It is the third-leading cause of death worldwide [2] and is responsible for high levels of health care use because of frequent respiratory exacerbations [3]. Individuals with COPD experience significant airflow obstruction and dynamic hyperinflation of the lungs, leading to symptoms of dyspnea, sputum production, chronic cough, and fatigue [1]. Skeletal muscle dysfunction, comprising decreased muscular strength and endurance, is also a common consequence of COPD and is driven by a combination of several mechanisms, including muscle atrophy, altered fiber type, and impaired metabolism [4]. Collectively, these changes contribute to diminished exercise capacity, limitations in activities of daily living (ADLs), and reduced health-related quality of life (HRQL) among individuals with COPD [5].

### Cognitive Impairment in COPD

A growing body of research has demonstrated the presence of limitations across several domains of cognition among individuals with COPD [6]. Decreases in attention, memory, and visual-motor processing have been commonly reported [6-8]. The underlying mechanisms of cognitive impairment among individuals with COPD are complex and have been attributed in part to neural tissue hypoxemia and systemic inflammation [9,10].

Recent studies have indicated that COPD is associated with impaired dual-tasking performance [11,12]. Dual tasking, the performance of 2 tasks simultaneously, is an important aspect of executive function and is often required for the performance of routine daily activities, such as walking and talking. The performance of a cognitive task (eg, spelling words backward) while carrying out a physical task (ie, usual-paced walking) can result in decrements in cognitive or physical performance (eg, walking speed or distance) owing to competing attentional demands. Dual task decrements (difference between dual and single task performance) are often more pronounced in those with existing cognitive impairments or neurological conditions compared with those without these disorders [13,14]. Indeed, increased dual task decrements for both motor [12,15] and cognitive [16] performance have been found among people with COPD compared with healthy individuals [17]. There is emerging evidence indicating that cognitive-motor dual task performance impairment among patients with COPD is related to alterations in markers of prefrontal cortex neural activity and inefficiency, which may impede the executive function needed to *plan one’s day* [11,12,17]. Thus, combined cognitive-physical training may be a good strategy to improve neural efficiency in patients with COPD who may have a range of executive functional capacities. Cognitive training targeting attention, memory, executive functioning, and speed of processing when combined with physical exercise training may provide the neuroplasticity to derive synergistic benefits on the performance of ADLs and physical function [18-20].

### Traditional Pulmonary Rehabilitation

Pulmonary rehabilitation is considered a primary management approach for moderate to severe COPD and has been shown to reduce dyspnea and increase exercise capacity, leading to improvements in daily function and HRQL among individuals with COPD [21]. To date, pulmonary rehabilitation strategies have typically focused on education (eg, medication management, breathing techniques, and stress reduction) and physical training (ie, aerobic and strength exercises) [21,22]. Currently, cognitive training is not included in most pulmonary rehabilitation programs despite evidence that cognitive impairments are common among individuals with COPD and are associated with greater functional limitations, decreased HRQL, and increased health care use in this population [8,23].

### Home-Based Pulmonary Rehabilitation

Several barriers limit engagement in pulmonary rehabilitation for people with COPD, including factors related to the environment (eg, travel and wait times), knowledge (eg, referral processes), and beliefs (eg, perceived benefits) [24]. Recently, accessibility has been further complicated by the COVID-19 pandemic. For these reasons, there is increasing interest in home-based pulmonary rehabilitation programs as an alternative strategy for COPD management compared with center-based pulmonary rehabilitation programs [25-27]. Several studies have demonstrated the safety and feasibility of remote telerehabilitation interventions for patients with COPD, with high levels of compliance with home training and no adverse events [28-30]. There is meta-analytic evidence from systematic reviews also indicating that the effects of home-based pulmonary rehabilitation interventions are similar to those of traditional outpatient programs for outcomes including dyspnea [26,27], exercise capacity [26,31], and HRQL [26,31], potentially offering increased accessibility to those with travel restrictions [32]. However, most studies on telerehabilitation for COPD have required study assessments to be conducted in person, and none have included remote assessment of functional testing, cognitive assessments, or dual task performance, a knowledge gap that this study hopes to address [27].

### Study Purpose

The specific aims of this study are to evaluate the feasibility (ie, recruitment rate, program adherence, attrition, safety, and participant satisfaction) of an 8-week individualized, home-based cognitive-physical training program for patients with moderate to severe COPD and derive preliminary estimates of cognitive-physical training intervention efficacy on measures of cognitive and physical function, dual task performance, ADL, and HRQL. We hypothesize that it will be feasible to safely recruit patients with COPD into a home-based cognitive-physical training program with 75% adherence and high satisfaction ratings with the prescribed training. We also hypothesize that the cognitive-physical training group will demonstrate greater beneficial effects on cognitive function, dual task performance, ADL, and HRQL compared with the physical training group.

## Methods

### Design

This is a pilot randomized controlled trial (RCT) to assess the feasibility of a full-scale, adequately powered RCT evaluating a home-based combined cognitive-physical training program for patients with moderate to severe COPD. The study takes place at the University Health Network (UHN) in Toronto, Ontario, Canada, but has been expanded to include recruitment from community respirology clinics not affiliated with the UHN.

### Ethics Approval and Informed Consent

Research ethics approval was obtained through the research ethics board of the UHN (study ID: 21-5336), and the study has been registered at ClinicalTrials.gov (NCT05140226). Informed consent will be obtained from participants before study enrollment.

### Participants

The study sample will consist of older adults (aged ≥50 years) with a clinical and spirometric diagnosis of moderate to severe COPD (postbronchodilator forced expiratory volume in the first second [FEV_1_]/forced vital capacity of <0.70 [or lower limit of normal of FEV1/forced vital capacity] and FEV_1_=30%-79%). Participants will be required to have access to a reliable internet connection and be able to mobilize independently and safely with or without a walking aid. Exclusion criteria include the following: (1) current participation in supervised in-person or an internet-based pulmonary rehabilitation program; (2) COPD exacerbation in the previous 3 months to ensure clinical stability; (3) presence of cardiovascular, neurological, or musculoskeletal conditions that could interfere with the safe performance of study procedures (eg, unstable coronary artery disease, heart failure, stroke, myopathy, or moderate to severe arthritis); (4) severe cognitive impairment ascertained through chart review or self-report (eg, severe dementia or inability to perform ADLs independently); (5) medical instability (eg, hepatic dysfunction, metabolic abnormality, or active infection); (6) overt psychiatric disorder or substance abuse; (7) current use of home oxygen therapy; (8) insufficient English fluency to carry out testing and training; and (9) being listed for lung transplantation.

### Recruitment and Screening

Participants will be recruited during routine visits to outpatient respirology clinics at UHN in Toronto, Ontario, Canada, and local respirology clinics. Clinic personnel within the circle of care will introduce the study to patients with COPD and ask if they are interested in participating. If interested, a member of the research team will then contact the potential participant to screen for eligibility criteria, review study procedures, and obtain informed consent. The study recruitment poster will also be provided to medical personnel at local respirology clinics who will introduce the study to patients with COPD and instruct them to contact the research team if they are interested in pursuing study participation.

### Study Timeline

The study timeline is shown in Figure 1. After completing consent procedures, participants will receive a package by mail containing the following study equipment: Fitbit Charge 4 device (Fitbit Inc), foot peddler (VANGONA D2 pedal exerciser), pulse oximeter, resistance bands (Thera-Band), measuring tape, and exercise manual. They will also receive an email with instructions on how to access the internet-based appointment platform (Microsoft Teams; Microsoft Corp) on their devices. Following receipt of study materials, participants in both groups will be booked for a 45-minute videoconferencing familiarization session. During the familiarization session, participants will be introduced to the study equipment and software, their safety in performing remote physical testing will be assessed, and study assessment procedures will be explained. Furthermore, appropriate equipment setup for remote testing will be determined, and participants will have the opportunity to practice the physical assessment tests. After the familiarization session, participants will be booked for the *baseline assessment* session (1 hour) to complete the assessment measures described in the following sections.

**Figure 1 figure1:**
[figure not shown]
Study timeline. COPD: chronic obstructive pulmonary disease; MRC: Medical Research Council.

### Randomization

After the baseline assessment, participants will be randomized to either the cognitive-physical training (intervention) group or the physical training (control) group using a 1:1 ratio. Randomization will be performed using shuffled opaque envelopes containing the group assignment. Given the pilot stage of this research and the nature of exercise interventions, group allocation will be known to the research team, exercise professionals, and study participants.

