**Test period**
Participants will continue pedaling at a set speed of 50 revolutions/minute and a resistance setting that allows them to carry on a conversation (approximately 3-4 on the Borg Rating of Perceived Exertion Scale) for as long as they can up to a maximum of 15 minutes. Participants will be prompted every few minutes to monitor their heart rate and oxygen saturation using an oximeter and their Borg Dyspnea score. The test will be stopped based on any of the following stopping criteria:15 minutes have been completed.Oxygen saturation drops to <85%.Self-reported Borg Dyspnea score is >7.The activity becomes unbearable (eg, severe leg pain or the participant is too tired to continue).Heart rate reaches 85% of age-predicted maximum (calculated as 220 beats/minute–age).Participant is unable to maintain a speed of 50 revolutions/minute.The research team member decides to stop the test because of apparent breathlessness or discomfort of the participant.

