##### Dual Task Performance

Dual task performance will be evaluated through a dual task test on the foot peddler, as previously undertaken in other populations [46,47]. Participants will complete a motor, cognitive, and combined dual task (all of 1-minute duration) in random order: (1) the *cognitive task* involves spelling 5-letter words backward from a list of 100 words provided verbally (homonyms excluded), (2) the *motor task* involves pedaling on the foot peddler at a set speed of 50 revolutions per minute and a self-selected resistance corresponding to a moderate-intensity level allowing participants to hold a conversation (approximately level 4 on the Borg RPE Scale), and (3) the *dual task* involves spelling and pedaling at the same time. Participants will be instructed to prioritize both tasks equally. Spelling tasks (single and dual tasks) will be audio recorded using a Dictaphone to allow for precise scoring. The number of words correctly spelled backward and the distance covered while pedaling will be compared between the single and dual task conditions to calculate a dual task cost score for both the cognitive and physical performance tasks.

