### Limitations

We also acknowledge that there are limitations to the design of this study. Given the small sample size, we will be unable to adjust the analyses for potential confounders such as medications (opiates, sedatives, or corticosteroids) or COPD exacerbations; however, these factors will be tracked throughout the study period to explore their influence on selected outcomes. This study will be conducted entirely remotely, and therefore, we are unable to prospectively measure specific tests of outcomes such as pulmonary function (ie, spirometry) or neural activity (ie, functional near-infrared spectroscopy). However, some of this information will be derived from chart review or will require future study. Furthermore, cognitive assessments will be completed independently at home, and differences in device or screen size (ie, computer vs tablet) may influence the results. Participants who do not have access to a suitable device will be provided with a tablet for the duration of the study. Owing to the nature of the training intervention and internet-based environment, blinding of participants and the exercise professional is not possible, thus creating a risk of bias. Furthermore, most of the physical training measures and intensity will be ascertained through self-report, which may not be as accurate as if they were captured electronically from the training devices.

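### The backward-spelling recordings could be scored without knowledge of arm or visit at almost no cost, but the plan leaves the whole research team aware of allocation and gives no reason for unmasked scoring

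*Protocol article*

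**What the plan says.** In the protocol article, Randomization opens its statement on masking with a reason, "Given the pilot stage of this research and the nature of exercise interventions", and concludes that "group allocation will be known to the research team, exercise professionals, and study participants". Limitations returns to the subject and says that "blinding of participants and the exercise professional is not possible, thus creating a risk of bias".

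Under Dual Task Performance, participants do a cognitive task (spelling five-letter words backward), a motor task (pedaling) and both together, each for 1 minute. On scoring, the section says: "Spelling tasks (single and dual tasks) will be audio recorded using a Dictaphone to allow for precise scoring". The outcome has two halves: "The number of words correctly spelled backward and the distance covered while pedaling will be compared between the single and dual task conditions", giving a dual-task cost for each.

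Dual-task performance is a secondary outcome, measured at baseline, week 4 and week 8. Randomization follows the baseline assessment. Data Analysis says that the secondary outcomes are summarized within and between groups so that the estimates can serve the sample size calculation of a larger trial. No section provides for a masked assessor or scorer, and none names the person who scores the recordings.

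**The concern.** The two reasons given for open allocation do not reach the scoring of an audio file. The nature of an exercise program explains why the person training and the person coaching know the arm. It does not explain why someone who later counts correct words from a recording needs to know it. The pilot stage is a reason for choosing a simple design, not an obstacle to masking.

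Dual-task performance is named in the Study Purpose hypothesis. The Discussion stresses that the cognitive training differs from the dual-task test, so that a gain on the test would suggest transfer to daily activities. By contrast, the BrainHQ assessment is modeled on the training exercises. The dual-task result is therefore one of the more informative secondary estimates that the pilot will hand on. If a scorer who knows the arm or the visit resolves doubtful words in one direction, the error goes straight into that estimate, and nothing in a later analysis can remove it.

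**Working it through.** The article states no figure on this point, so the check is mainly a comparison of sections.

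1. **Who knows the arm.** Randomization: the research team, the exercise professionals and the participants.
2. **For whom blinding is called impossible.** Limitations: participants and the exercise professional. Testers and scorers are not mentioned either way.
3. **Who tests and scores.** The physical function sections and Textbox 1 show the research team running the remote tests. The scorer of the recordings is not named. That the scorer belongs to the team that knows allocation is an inference, though a natural one.
4. **What can be masked.** The spelling tasks, single and dual, are recorded. Pedaling distance is not stated to be recorded. Masked scoring is therefore available for the cognitive half of the outcome and not, on the text, for the motor half.
5. **Which visits are exposed.** Baseline testing precedes randomization, so the conduct of that test cannot be influenced by the arm. The article does not say that baseline recordings are scored before allocation is known, so their scoring could be influenced. For this reason all three visits belong in the masked set.
6. **Where the estimate goes.** Data Analysis: into the planning of a larger trial.

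Could the pilot's own data reveal a scoring shift? This is an illustration on assumed shifts, because the document gives neither an SD nor a bias size.

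- Completers per group, from Sample Size: 12 × (1 − 0.20) = 9.6, taken as 10.
- Half-width of the 95% CI for a difference between groups, in SD units: t(0.975; 18) × √(2/10) = 2.101 × 0.447 = 0.94. It is 1.00 with 9 per group and 0.85 with 12.
- If there were no true effect and scoring favored one arm by 0.1, 0.2, 0.3 or 0.5 SD, a two-sided t test would reject in about 5.5%, 7.1%, 9.7% or 18.5% of trials instead of 5%. The 5% level is assumed to match the 95% CIs, since no level is stated.

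A shift of a few tenths of an SD would thus be lost inside the interval while still moving the point estimate by its full amount. These figures do not show that such a shift will occur.

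**The case against.** The best defense is that the open design is disclosed and deliberate. Randomization states it with reasons, and Limitations acknowledges a risk of bias from lack of blinding. The outcome is secondary, no power calculation was made for it, and no feasibility criterion depends on it. Standard operating procedures are said to exist for all procedures, and these may name a scorer. Spelling a listed five-letter word backward is close to right or wrong, which leaves little room for judgment. All of this stands and limits the weight of the point. It does not supply a reason for leaving the scoring of existing recordings unmasked.

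Three stronger readings are tempting and are not supported.

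- **That the two sections contradict each other.** A reader might infer from Limitations that everyone else could be blinded. It names two roles and is silent on the rest, which is compatible with a choice to leave staff unmasked.
- **That one doubtful word would move the dual-task cost by 8 to 17 percentage points.** This follows from 1/12 and 1/6 if 6 to 12 words are correct on the single task, but the article gives no word counts and no formula for the cost. It also requires an error on the dual-task recording alone. Take cost as (single − dual)/single. One word credited on both recordings changes 12/10 to 13/11, so the cost goes from 16.7% to 15.4% (1.3 points). It changes 6/5 to 7/6, from 16.7% to 14.3% (2.4 points). The error would also have to recur across one arm to become a bias between groups.
- **That staff discretion to end the endurance test is a defect.** It is one of seven listed stopping criteria and reads as a safety provision, and the reason for ending the test is already recorded.

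Masked scoring is also only a partial remedy. It leaves the live delivery of the words, the pedaling distance and the participants' own knowledge of their arm as they are. In a trial of 24 people with weekly video calls, a team member may recognize a voice.

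**Conclusion.** The point holds as a cheap improvement. The article makes allocation known to the whole research team, gives reasons that do not extend to scoring, and already creates the recordings that would permit masked scoring of the spelling half of the dual-task outcome. The conclusion assumes that the scorer comes from the team that knows allocation, which the text implies without stating.

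The size of any bias cannot be derived from the document and may be small. The primary conclusions on recruitment, retention, adherence, safety and satisfaction are unaffected. What gains protection is one secondary estimate, which the plan itself intends to carry into the next trial.

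**What to change.** Add to Dual Task Performance that all spelling recordings (single and dual task, from baseline, week 4 and week 8) are given codes that show neither arm nor visit, are placed in random order, and are scored by an existing team member who does not run that participant's weekly calls or assessments. Qualify the sentence in Randomization accordingly.

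Add to Limitations that the remaining live assessments, such as pedaling distance and the endurance test, are carried out unmasked.

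No new staff, visits, equipment or participants are needed, and the sample size does not change. The cost is the time to recode and shuffle the files. The one weakness is that masking fails where a voice is recognized, which choosing a scorer without contact with that participant makes less likely. Recordings already made can be handled in the same way, provided that they have been kept.
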